### MAHA intervention

The MAHA model is a patient- and family-centered system in which care is tailored around the complex, chronic needs of those with progressive disabling MS. The intervention program is designed to address a fundamental question: “how will this affect the patient and/or family?” The majority of care and medical services will be provided at home, thus avoiding frequent and cumbersome clinic visits. The intervention strategies were developed based on the frequent requests and suggestions from patients with progressive MS, along with caregivers and providers experiencing daily struggles with fragmented care. Furthermore, the model is also supported by initiatives from the health policy literature developed by the National Multiple Sclerosis Society (NMSS), emphasizing the need for home- and community-based services (
http://www.nationalmssociety.org/Treating-MS/Comprehensive-Care).

***MAHA Team Structure.*** The intervention will be delivered by a transdisciplinary team led by a MS-Comprehensivist, also referred to as Care Team Leader (CTL). The care provided is comprehensive and holistic, addressing patient/family physical, emotional and spiritual, and social needs. The transdisciplinary team includes the core team partners and “neighbors and best friends” (
Figure 2). The CTL role will be filled by a nurse practitioner (NP) with specialty training in MS and extensive experience managing patients with chronic illness. The core team partners include the CTL, MS neurologist, primary care provider (PCP), and selected home health agencies. To address MS patients’ complex needs and reduce unplanned healthcare services, the CTL will closely collaborate with patients and family, the MS neurologist and the PCP to develop patient-centered care plans and goals, and to co-manage symptoms and complications. The selected home health agencies will provide nursing and personal care staff, physical and occupational therapists (PT/OT), and social work services. They are responsible for carrying out the care plan and conducting collaborative, on-going evaluation of the care plan with the CTL. Given MS patients’ limitations in mobility, PT/OTs will also be involved in plans of care to facilitate the restoration and maintenance of function oriented toward activities of daily living (ADLs). PTs from the home health agencies will be trained by physical therapists who have extensive experience in the education and care of MS patients. “Neighbors & Best Friends” represent subspecialty providers and community resources. The “neighbors”, or subspecialty providers (e.g., urologist, rehabilitative professionals, palliative care specialist, ophthalmologist, wound care specialist, etc.) provide consultation services and advise the CTL in preventative and treatment strategies for common complications or issues not responsive to standard strategies. The “Best Friends”, include community resources, including clergy, respite services, the MS Society, League of Human Dignity, and Office on Aging, among others.

**Figure 2. f2:**
[figure not shown]
MAHA Model.

***MAHA Team Processes (10 C’s).*** The MS-Comprehensivist or CTL will be responsible to: 1) provide regular and frequent visits to patients’ homes using a pre-planned schedule based on each individual’s care needs; 2) coordinate patients’ care by collaborating and communicating closely with the core team partners, and “neighbors and best friends”; and 3) train the home health staff in the specialty care of MS patients. In the process of care, the MAHA model stresses patient/family engagement (i.e., informed and activated) and productive interaction between patients and providers through ten fundamental elements (10 Cs;
Figure 3).

**Figure 3. f3:**
[figure not shown]
Ten fundamental elements guiding the care process.

### Data collection, instruments and sources of data

Key data collection instruments, assessments, and measures are summarized in
Table 1. This information will be collected from three data sources: 1) patient reports to CRC personnel, 2) patient reports to the CTL or other MAHA team member at each home visit, and 3) medical record review.

**Table 1. T1:** Study measures.

Data Collection Instrument/Assessment		Method, Location, Data Source	Measure Timeline (in months)								
			BL*	3	6	9	12	15	18	21	24
Kurtzke Expanded Disability Scale (EDSS)		Neurologist/CTL to assess in person	X				X				X
PATIENT REPORTED MEASURES											
-Demographics		CRC to collect at baseline visit and via mail/phone	X								
-Functional activity of daily livings (ADLs) (Barthel) ^42^			X	X	X	X	X	X	X	X	X
-Multiple Sclerosis QoL Inventory (MSQLI) ^43^			X				X				X
-Novak Caregiver Burden Inventory (CBI) ^44^			X	X	X	X	X	X	X	X	X
-Client Satisfaction Questionnaire (CSQ-8) ^45^			X		X		X		X		X
POTENTIAL COMPLICATONS											
-Pneumonia -Urinary Tract Infection (UTI)	-Falls -Pressure Ulcer	CRC to collect at baseline visit, via mail/ phone and from medical record review. Providers assess during in-person visits	X	X	X	X	X	X	X	X	X
HEALTH SERVICES USE											
Emergency Room (ER) -Unplanned (acute)	Inpatient Admissions -Planned (elective) -Unplanned (acute) -Length of Stay	CRC to collect at baseline visit and via mail/phone. Providers assess during in-person visits. Data are retrieved from medical record.	X	X	X	X	X	X	X	X	X
CPT Codes and Reimbursement Amounts		UNMC Neurology Clinic Database	X		X		X		X		X
MAHA RESOURCE INTENSITY											
-Home visit time logs -On-call activity logs -Coordination care management activities		MAHA staff to document after each home visit and on-call activity	X	X	X	X	X	X	X	X	X

**Baseline questionnaires will be performed at the baseline clinic visit*

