## Methods

### Study design

The study is a prospective, two-group, randomized experimental design with nine data collection points (baseline and every three months). MS patients recruited from a neurology clinic will be randomized into two groups: the intervention or usual care group. The usual care group receives the current standardized MS care, while the intervention group receives usual care plus 24-months of the MAHA intervention provided by a transdisciplinary team led by a MS-Comprehensivist. The usual care group will receive the intervention at the end of the 24-month period if the intervention is found to be effective by our a priori criteria. The study is subject to review and approval by the University of Nebraska Medical Center Institutional Review Board (IRB) and informed consent will be obtained from all participants prior to the study.

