***Specific Aim 3.*** To assess the acceptability, utility, implementation and adaptation of the program, we will create a toolkit that comprehensively describes our program structure, processes, patients/provider/system outcomes, as well as lessons learned. This toolkit will serve to evaluate the MAHA program and identify system-, provider-, and patient-levels of barriers and facilitators. To evaluate financial sustainability, we will specifically track the Current Procedural Terminology (CPT) codes for evaluation and management visits (clinic and home visits), care coordination, and care plan oversight. Reimbursement amounts associated with these codes will be summed for each study group at six and 12 months. T-tests and log transformed linear regression models will be used to compare total reimbursement amounts between groups. Also, staffing and associated salary estimates will be computed based on home visit time logs maintained by the MAHA team members, on-call activity logs, and number of home visits in the intervention group. We will project the necessary percent FTE and salary to execute the intervention model based on a range of panel sizes (e.g., 25, 50, 100 patients) per MS-Comprehensivist/CTL. The ratio of total salary costs-to-reimbursement amount for a given number of patients will be calculated for each group and compared using t-tests.

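### Home-visit reports, which only the MAHA arm can generate, are a named source for the event counts, and nothing keeps them out of the between-group comparison

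*Protocol article*

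**What the plan says.** The section on data collection, instruments and sources of data gives three sources for everything in Table 1: patient reports to CRC personnel, "2) patient reports to the CTL or other MAHA team member at each home visit", and medical record review.

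For complications (pneumonia, urinary tract infection, falls, pressure ulcer), Table 1 states: "CRC to collect at baseline visit, via mail/ phone and from medical record review. Providers assess during in-person visits". The health-services-use row likewise lists CRC contact, provider assessment and the medical record. Both rows are marked at baseline and every three months to month 24, with no restriction by arm.

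On who gets home visits, Study design says: "The usual care group receives the current standardized MS care, while the intervention group receives usual care plus 24-months of the MAHA intervention". Under MAHA Team Processes, the team leader is to "provide regular and frequent visits to patients’ homes using a pre-planned schedule based on each individual’s care needs". The Specific Aim 3 analysis refers to the "number of home visits in the intervention group".

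Data analysis compares complications between groups with a linear mixed model and unplanned utilization with Poisson regression. Neither description mentions the source of an event.

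**The concern.** A between-group comparison of event counts is fair only if an event has the same chance of being recorded in either arm. Here one of the three named sources has no usual-care counterpart. Its visits follow individual need rather than the quarterly schedule, so the patients with the most problems may be observed most often.

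The complication count in Specific Aim 1 is the most exposed. A fall without injury, a mild urinary infection or an early pressure ulcer may be known only because someone asked or looked. Randomization, intention-to-treat analysis and covariate adjustment do not correct a difference in detection. If sources are not flagged when events are collected, they may not be separable later.

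**Working it through.** **1. Sources by arm**

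| Source | MAHA | Usual care |
|---|---|---|
| CRC contact by mail/phone | quarterly | quarterly (no arm restriction stated) |
| Medical record review | yes | yes |
| Reports to MAHA staff at home visits | at each visit | none |
| Provider assessment in person | yes | possibly, at clinic visits |

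The third row is the asymmetry, and it is stated in the article rather than inferred from a gap.

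**2. The plan's own figure**

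Inputs from Sample size: 2.5 versus 1.65 unplanned visits or admissions per person per year, so RR = 1.65/2.5 = 0.66; 5% significance; 80% power; 50 per group. My assumptions are a two-sided test, one year per person and Poisson counts without overdispersion. The abstract speaks of fifty patients in all, which is a separate matter; I use 50 per group.

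- n per group = (1.960 + 0.842)² × (1/2.5 + 1/1.65) / (ln 0.66)² = 7.849 × 1.006 / 0.1727 = 45.7, so 46.
- At 50 per group, SE = √(1.006/50) = 0.142 and power = Φ(0.4155/0.142 − 1.960) = 83%.

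The claim of 80% power with 50 per group is met.

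**3. Effect of unequal capture**

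Observed RR = true RR × (capture in MAHA / capture in usual care). The documents give no capture rates. I assume 100% in MAHA and vary usual care. Power uses the formula above, with the usual-care rate multiplied by its capture and MAHA at 1.65.

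| Usual-care capture | Observed RR (true 0.66) | Power, 1 year | Power, 2 years |
|---|---|---|---|
| 100% | 0.66 | 83% | 98.5% |
| 95% | 0.66/0.95 = 0.695 | 72% | 95% |
| 90% | 0.66/0.90 = 0.733 | 57% | 86% |
| 80% | 0.66/0.80 = 0.825 | 25% | 45% |

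If the true RR is 1 (2.5 per year in both arms), 90% and 80% capture give observed ratios of 1.11 and 1.25. The chance of a significant result against MAHA is then 12.5% and 38% over one year, or 21% and 65% over two, against a nominal 2.5%.

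**4. What the table does and does not show**

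The 0.66 is the only planned rate ratio in the article, and it belongs to visits and admissions, where a large capture gap is least plausible. No planned rate is given for falls, infections or ulcers, where the gap could be largest. The table shows how a gap acts on a rate ratio; it does not estimate this trial's bias.

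**5. Direction**

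If the sources are combined, a further source in one arm can only add events there. The expected distortion is therefore an inflated MAHA count.

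**The case against.** The strongest reply is that ascertainment common to both arms is already planned: "CRC to collect at baseline visit, via mail/ phone and from medical record review", repeated quarterly. This stands, and it limits the bias. It protects ER visits and admissions best, since those leave records. It protects less well against missing events that produce no record and depend on recall.

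Second, "Providers assess during in-person visits" does not name the MAHA team, and usual-care patients may be examined at clinic visits. That is a fair reading of Table 1. The list of sources, however, does name the MAHA team and home visits.

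Third, the article does not say how the three sources combine into the analysed count, and a fuller document may settle that. This also stands. A reader might infer that the counts are certainly pooled and therefore certainly biased. Pooling is the natural reading of one body of information drawn from three sources, but it is not stated, so the supportable claim is that the counts could be biased.

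A reader might also infer that unblinded MAHA staff could create a false benefit by under-recording. The documents do not support this. An event that MAHA staff leave out can still reach the count through the CRC or the medical record. Their silence would lower the count only if their reports replaced those sources, and the article does not say that.

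**Conclusion.** The concern holds in a limited form. A source available to one arm only is named for the outcome measures, and the article does not confine the between-group counts to shared sources. Detection of falls, urinary tract infections and pressure ulcers could therefore be higher under MAHA, mainly masking a real reduction. The effect on ER visits and admissions should be smaller, so the two sets of outcomes should not be treated as equally exposed.

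The size cannot be derived from the documents. The shift from 0.66 to about 0.73-0.83 rests on an assumed 10-20% shortfall in usual-care capture and on the same capture for all events within an arm.

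**What to change.** State that the main Specific Aim 1 complication counts and Specific Aim 2 utilization counts come from two sources only:

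- the quarterly CRC contact, with the same questions and recall window in both arms;
- review of records not generated by the MAHA team.

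The second limit is needed because the team leader is a nurse practitioner whose home visits are tracked by billing code. Visit notes would plausibly enter the medical record, and unrestricted record review would then bring the asymmetry back.

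Record the source of every event. Keep events known only from MAHA home visits or MAHA visit notes for process reporting or a sensitivity analysis. Settle this before data collection.

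The cost is a source field on the event form, a rule for the record reviewers and a sentence in the analysis section; the CRC contacts and record review are already planned. There are two downsides. Some true events leave the main count. Some asymmetry also remains, because a patient told of a condition at a home visit may report it to the CRC.

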### Data analysis

***Specific Aim 1 and 2.*** The data analysis will follow the intention-to-treat (ITT) protocol. To ensure groups are comparable, descriptive analyses, including t-tests and Chi-square tests will be conducted to compare the characteristics of each group at baseline. The occurrence of complications and other self-reported measures, such as ADLs, Multiple Sclerosis QoL Inventory (MSQLI), CSQ-8, and Caregiver Burden Inventory (CBI) will be compared between groups using a linear mixed model to account for the repeated measurements over time and adjust for baseline scores of the respective measures. To determine if differences exist between groups after adjusting for potential confounding variables, such as age, gender, comorbidity, etc. or imbalances between groups, unplanned healthcare utilization (i.e., visits/admissions) will be analyzed using Poisson regression models. The proportion of any versus no use of each health service (e.g., proportion with any inpatient admissions versus the proportion with no admissions) will be compared between groups using Chi-square tests. The time-by-group interaction will be investigated to determine if any changes over time are consistent between groups.

***Specific Aim 3.*** To assess the acceptability, utility, implementation and adaptation of the program, we will create a toolkit that comprehensively describes our program structure, processes, patients/provider/system outcomes, as well as lessons learned. This toolkit will serve to evaluate the MAHA program and identify system-, provider-, and patient-levels of barriers and facilitators. To evaluate financial sustainability, we will specifically track the Current Procedural Terminology (CPT) codes for evaluation and management visits (clinic and home visits), care coordination, and care plan oversight. Reimbursement amounts associated with these codes will be summed for each study group at six and 12 months. T-tests and log transformed linear regression models will be used to compare total reimbursement amounts between groups. Also, staffing and associated salary estimates will be computed based on home visit time logs maintained by the MAHA team members, on-call activity logs, and number of home visits in the intervention group. We will project the necessary percent FTE and salary to execute the intervention model based on a range of panel sizes (e.g., 25, 50, 100 patients) per MS-Comprehensivist/CTL. The ratio of total salary costs-to-reimbursement amount for a given number of patients will be calculated for each group and compared using t-tests.

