### Sample size

The sample size estimation is computed based on
**Specific Aim 1**: the increased score of quality of life (QoL) and
**Specific Aim 2**: the reduced number of unplanned healthcare utilizations associated with complications. An estimated 50 patients per group will provide 80% power to detect a 5-point difference [Usual Care mean (SD): 45(8.6), MAHA mean (SD) 50(8.6)] between groups in the SF-36 Mental Health Component Score QoL. This sample size also provides 80% power at a 5% significance level to detect a 34% reduction in unplanned visits/admits (from 2.5 per person per year to 1.65, using the Poisson distribution, which is most appropriate for count/rate data). These are feasible and clinically important differences. Based on our preliminary analyses, 125 patients are currently expected to meet these criteria. Furthermore, based on our previous patient survey results, a high proportion of patients (~80% or n = 100) have expressed a genuine interest in participating in MS research for the benefit of others with this disabling disease. Furthermore, we estimate 50 patients will be a reasonable panel size for the MS-Comprehensivist or care team leader (CTL) in the MAHA model (unpublished report).

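### The covariate set for the utilisation model is open and partly set by observed imbalance, and the baseline utilisation count already collected is not named in it

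*Protocol article*

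**What the plan says.** All the analysis wording is in one paragraph of the Protocol article, Data analysis, under Specific Aims 1 and 2.

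- **Baseline comparison.** "To ensure groups are comparable, descriptive analyses, including t-tests and Chi-square tests will be conducted to compare the characteristics of each group at baseline".
- **Complications and self-reported measures.** These are compared "using a linear mixed model to account for the repeated measurements over time and adjust for baseline scores of the respective measures".
- **Utilisation.** "unplanned healthcare utilization (i.e., visits/admissions) will be analyzed using Poisson regression models", the purpose being to find group differences after "adjusting for potential confounding variables, such as age, gender, comorbidity, etc. or imbalances between groups".

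Table 1 (Data collection, instruments and sources of data) marks emergency room visits and inpatient admissions at baseline and at every quarter. The stated method is "CRC to collect at baseline visit and via mail/phone. Providers assess during in-person visits. Data are retrieved from medical record". The look-back period of the baseline count is not given.

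The Sample size section powers the utilisation comparison for a fall "from 2.5 per person per year to 1.65, using the Poisson distribution, which is most appropriate for count/rate data".

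**The concern.** Three features of that paragraph need attention.

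1. **The tests cannot do what they are planned for.** In a properly randomised trial the null hypothesis of a baseline test is true by design. A significant result flags a chance event and a non-significant one does not show that the groups are alike.
2. **The covariate set is not closed.** The named variables are examples, the list is open-ended, and an alternative route admits whatever turns out to be imbalanced. The last clause can only be applied once data by arm have been seen. The utilisation comparison makes up the whole of Specific Aim 2 and is one of the two bases for the sample size, so its rate ratio should not depend on choices made at that stage.
3. **The two models are treated differently.** The mixed model carries the baseline value of each outcome. The utilisation model names age, gender and comorbidity but not the baseline count of the same events.

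At stake are the type I error of the Aim 2 comparison, if the adjustment set can be chosen with results in view, and possibly some precision.

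**Working it through.** **Inputs.** From the Sample size section: 50 per group, rates 2.5 and 1.65 per person-year (ratio 0.66), 5% significance (taken as two-sided), 80% power. From Study design: 24 months of follow-up. Assumed, because the article gives neither: the between-patient variance k of the underlying event rate, and the baseline look-back. (The Abstract gives fifty patients in all; 50 per group is used here because the power statement rests on it.)

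**1. The article's own figure.** With a Wald test on the log rate ratio and T years of follow-up,

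n per group = (1.960 + 0.842)² × (1/2.5 + 1/1.65) / (T × ln(0.66)²).

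For T = 1 this is 7.849 × 1.006 / 0.1727 = 45.7, so 46 per group. Power at 50 per group is Φ(0.4155 / √(1.006/50) − 1.960) = Φ(0.97) = 83%. The stated 50 is reproduced, slightly on the safe side, for one person-year each and no variation between patients (k = 0).

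**2. Discretion over the covariate set.** Simulation under no treatment effect: 50 per group, one year, k = 0.5, eight independent baseline covariates of varying prognostic strength, Poisson regression with Pearson-scaled standard errors, 2,000 runs.

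| How the set is chosen | Type I error |
|---|---|
| Three covariates fixed in advance | 6.0% |
| Covariates with baseline p<0.05 | 4.4% |
| Most favourable of 12 sets | 13% |

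The 12 sets are: unadjusted, p-selected, the fixed three, all eight, and each of the eight alone. The Monte Carlo standard error at 5% is √(0.05 × 0.95/2000) = 0.5 points. A mechanical rule does not inflate the error; free choice does.

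**3. Adding the baseline count.** Counts were drawn as gamma-Poisson with the same patient rate before and after baseline, and analysed without and with log(baseline count + 0.5). Rate ratio 0.66, 50 per group, 1,500 runs, scaled standard errors. Entries are power without → with the baseline count.

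| Assumed k | 1-year follow-up, 1-year look-back | 2-year follow-up, 1-year look-back | 2-year follow-up, 3-month look-back |
|---|---|---|---|
| 0 | 83% → 83% | 98% → 98% | 98% → 98% |
| 0.25 | 65% → 69% | 83% → 90% | 83% → 85% |
| 0.5 | 54% → 68% | 63% → 82% | 66% → 73% |
| 1 | 38% → 62% | 47% → 79% | 44% → 58% |

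Check on one unadjusted entry (k = 0.5, one year): SE = √((1.006 + 2 × 0.5)/50) = 0.200, and power = Φ(0.4155/0.200 − 1.960) = 55%, against 54% simulated.

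In this table the gain is nil at k = 0 and 2 to 32 points for k from 0.25 to 1. A separate simulation gave 1 to 29 points over the same range of k, so about 1 to 30 is a fair summary.

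**4. If patients' rates are not stable.** When half of the patients' rates change after baseline, the gain for k from 0.25 to 1 falls to between about −1 and 6 points, which at the low end cannot be told from zero.

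**The case against.** The strongest reply is that this is a condensed article. Final covariate lists and look-back windows normally sit in an analysis plan, which is not shown, so their absence is no fault. That stands for missing detail. It does not cover an imbalance clause that the article itself writes into the model, or a purpose for the baseline tests that they cannot serve. A later plan that followed this wording would inherit both.

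Four stronger readings are tempting and are not supported:

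- **That baseline p-values select the covariates.** The article calls the tests descriptive, gives no threshold or selection rule, and names age, gender and comorbidity in advance. The link from test to model would be an inference. Even a fixed p<0.05 rule gave no inflation in the simulation.
- **That the baseline count will be left out.** The Poisson sentence is silent on it. The open list could include it, and so could a repeated-count model if the planned time-by-group interaction extends to utilisation.
- **That power is being wasted.** Under the article's own Poisson assumption there is nothing to gain. The larger gains need sizeable variation between patients and rates that hold steady over 24 months, which is optimistic in a progressive disease.
- **That comorbidity is not collected because Table 1 has no row for it.** Table 1 summarises key measures only, and medical record review is a listed data source.

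It is also fair to say that the 13% describes an analyst choosing the best of 12 results, which the article does not plan. The figure is an upper illustration of what an open set permits, not a forecast.

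**Conclusion.** The point holds in a limited form. As written, the adjustment set for the Aim 2 utilisation model is open and partly dependent on observed imbalance, and the baseline significance tests have a purpose that they cannot meet in a randomised trial. These follow directly from the wording and need no assumption. The type I risk comes from discretion: about 13% in the worst case simulated, against 4.4% under a mechanical rule, both with eight assumed covariates and k = 0.5.

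That the baseline count is not named is an inconsistency with the mixed model in the same paragraph, not proof of exclusion. Naming it is worth nothing in power at k = 0, about 1 to 30 points for assumed k of 0.25 to 1 with stable patient rates, and roughly −1 to 6 points if half of the patients' rates change. The article gives neither k nor the look-back, so the size of the gain is uncertain. The case for naming the count is that it costs almost nothing and may help considerably. Confidence is good on the wording and only moderate on the power gain.

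**What to change.** Before outcome data by arm are seen:

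1. State a closed covariate set for the utilisation model: log(baseline utilisation count + 0.5), with a defined look-back window, plus a few named covariates, for example the article's own age and gender.
2. Delete the open ending of the covariate list and the clause on imbalances from the main analysis. Label any other adjustment as a sensitivity analysis.
3. Describe baseline characteristics by arm without significance tests, and drop the claim that testing ensures comparability.

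The cost is a few sentences and a look-back definition for data that Table 1 already collects. No patients, visits or instruments are added.

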^32^, leading to unnecessary healthcare utilization and delayed effective treatments
^33^. Without the comprehensive disease management by a designated provider, the quality of care received is often suboptimal or poor due to the fragmented care system in which the acute care based providers are unfamiliar with patients’ needs, have little knowledge and experience caring for patients with MS
^34^. The combination of the current ambulatory care system utilizes a fee-for-service payment model combined with shortage of MS care specialists leaves no time to address complex chronic care issues or advance care planning
^35–
37^.

To address these problems and gaps in inadequately caring for patients living with progressive MS, we propose a home-based, patient-centered, comprehensive care management program led by a ‘MS-Comprehensivist’. The program is designed to provide a full range of medical and social services for patients and their caregivers, including a transdisciplinary team of primary care providers, specialists, care managers, rehabilitative, social home health, and personal care services. The MS-Comprehensivist who is an advance practice nurse specialized in MS care is responsible to 1) make regular house calls to address patients/family specific needs, 2) coordinate the care with the primary and specialty providers, 3) identify and mobilize other community resources, and 4) provide staff training and patient education in co-managing the complex complications and symptoms. This program, referred to as
**M**ultiple Sclerosis
**A**t
**H**ome
**A**ccess (MAHA), incorporates core principles of the chronic care and patient-centered medical home models. The purpose of the proposed study is to examine the feasibility (e.g., acceptability, utility, implementation, financial sustainability, adaptation and integration)
^38^ and effect of the MAHA model on patient-centered outcomes (i.e., complications, quality of life, satisfaction) and health care utilization outcomes (i.e., unplanned hospitalization and ED visits). The following specific aims were designed to achieve this purpose.

**Specific Aim 1**: To evaluate the effect of the MAHA model on 1) the numbers of complications; 2) patients’ quality of life; and 3) patients’ satisfaction over time (baseline and quarterly).

**Specific Aim 2**: To evaluate the effect of the MAHA model on 1) the numbers of emergency room (ER) visits, and 2) the numbers of unplanned hospitalizations.

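### Complications, Aim 1's first outcome and defined there as a number, are put in a linear mixed model with the questionnaire scores, while the other event count gets Poisson regression

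*Protocol article*

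**What the plan says.** The Background section states Aim 1 as "To evaluate the effect of the MAHA model on 1) the numbers of complications", followed by quality of life and satisfaction, all followed quarterly. Table 1 lists four complications (pneumonia, urinary tract infection, falls, pressure ulcer), recorded at baseline and at each of eight quarterly points.

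In Data analysis, under Specific Aim 1 and 2, "The occurrence of complications and other self-reported measures" (ADLs, MSQLI, CSQ-8 and caregiver burden are the examples) "will be compared between groups using a linear mixed model to account for the repeated measurements over time", with adjustment for the baseline value. No count distribution or link function is named.

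The same paragraph says that unplanned visits and admissions "will be analyzed using Poisson regression models". The Sample size section sizes that outcome "using the Poisson distribution, which is most appropriate for count/rate data". The paragraph ends: "The time-by-group interaction will be investigated to determine if any changes over time are consistent between groups". That sentence names neither an outcome nor a scale.

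**The concern.** Quarterly complication numbers are small counts, probably with many zeros, and their variance rises with the mean. A linear mixed model in its plain reading assumes constant residual variance and an effect that adds or subtracts a fixed number of events. It returns a difference in mean counts, so the Aim 1 complication result cannot be set beside the Aim 2 utilisation result, which will be a rate ratio.

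The interaction is the more practical matter. Patients have progressive disease at EDSS 6.5 or above and are followed for 24 months, so a rising background rate is plausible. If MAHA then lowers the rate by the same proportion throughout, the absolute difference widens with time. A linear model would report an effect that changes over time, and a log-link model would report a stable one.

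This is not a gap left to an analysis plan. The article names the model, and an analysis plan that followed it would carry the mismatch forward.

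**Working it through.** **1. The plan's own figures.** The article gives no power figure for complications. Its figure of 50 per group concerns two other outcomes and is met, assuming a two-sided 5% level (the article does not state sidedness):
- Quality of life: n = 2(1.96 + 0.84)²(8.6/5)² gives 47 per group, or 48 with the t distribution.
- Utilisation, one person-year each: n = (1.96 + 0.84)²(2.5 + 1.65)/(2.5 − 1.65)² = 7.85 × 4.15/0.7225 ≈ 45.1, so 46 per group.

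The sample size therefore does not depend on this point.

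**2. Assumed inputs for complications.** The documents give no rate, trend or between-patient spread. Assumed: 0.3 events per patient-quarter at the start in usual care; a background rate that stays flat, doubles or triples over eight quarters; gamma-distributed patient frailty with shape k of 0.5 to 1; 50 per group. The rate ratio of 0.66 is borrowed from the 34% reduction used for utilisation.

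**3. Variance.** With gamma frailty, variance = μ + μ²/k. At k = 1 it is 0.3 + 0.09 = 0.39 when μ = 0.3, and 0.9 + 0.81 = 1.71 when μ = 0.9. That is a more than fourfold rise where the linear model assumes none.

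**4. Scale.** With a constant ratio of 0.66, the difference at 0.3 per quarter is 0.3 × 0.34 = 0.10 fewer events. At 0.6 it is 0.20 fewer, and at 0.9 it is 0.31 fewer. The ratio never changes, but the difference doubles or triples.

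**5. Rejection by the linear time-by-group test at 5%, constant ratio 0.66:**

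| Background rate | Random intercept | Random slope |
|---|---|---|
| Flat | about 5% | about 5% |
| Doubles | about 13% | about 8–10% |
| Triples | about 28–30% | about 14–18% |

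A wider grid (rates 0.3 to 0.6, frailty variance 0 or 1, 25 or 50 per group, 2,000 runs per setting) gives about 5%, 9–22% and 11–48% for the same three trends.

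**6. No treatment effect.** With a rising rate, a random-intercept-only fit rejects the interaction in about 7–14% of trials, because frailty multiplied by a trend makes patients' slopes differ and the model omits this. The random-slope form stays at 4.2–5.8%. The baseline-adjusted group comparison rejects in 3.7–5.9%.

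**7. Is plain Poisson the cure?** No. A Poisson test on patient totals that ignores between-patient variation has a type I error of 14–49% at frailty variance 1 (rates 0.1 to 0.6).

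**The case against.** The defence has several good points.

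- *A mean difference is a legitimate effect.* A reader might infer that the Aim 1 complication comparison is invalid. The documents do not support that: under randomisation the group test keeps its level.
- *The 14–30% figures are not false-positive rates on the additive scale.* If the ratio is constant and the background rises, the absolute difference really does change, and the linear model detects it. It misleads only a reader who takes it as a statement about the relative effect.
- *The article does not say that counts require a Poisson model.* It says "which is most appropriate for count/rate data", in a parenthesis about utilisation. It sets no rule for complications, though the reason it gives applies to them.
- *The size rests on an assumed trend.* With a flat rate nothing happens. At 25 per group, which the abstract's total of fifty would imply, the tripling scenario falls to roughly 20% (random intercept) or 10% (random slope).
- *The null inflation belongs to one random-effects structure.* The article states none, and that detail is commonly left to an analysis plan, so the inflation cannot be charged to the plan.
- *A linear model can handle unequal observation time*, through rates with weights. The lack of a stated offset is no fault in itself.
- *The interaction sentence follows the utilisation analyses* and is not tied to complications. It does close a paragraph headed Specific Aim 1 and 2, so reading it as covering both is natural.
- *Occurrence may mean yes/no per quarter.* Aim 1 favours a number. If yes/no was meant, a logistic model would be the natural counterpart, and the two sections disagree on what the outcome is.

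These points limit the harm. None explains why two event counts in one paragraph get different kinds of model.

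**Conclusion.** The concern holds in a limited form. The article defines complications as a number, then models them like a questionnaire score, against its own preference for count data and its own choice for utilisation. The consequences are an effect scale that cannot be compared with Aim 2 and an interaction result that depends on an unstated scale. The overall group test and the sample size are unaffected.

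The size is conditional. For a constant ratio of 0.66 and 50 per group, the chance of an apparent change in effect over time goes from about 5% (flat background) to about 8–13% (doubling) and 14–30% (tripling), depending on the random-effects form. The starting rate, trend and frailty are assumptions, and the ratio is borrowed from another outcome. The inconsistency between sections needs none of them. It should be corrected, but it does not undermine the trial.

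**What to change.** In Data analysis, take complications out of the linear mixed model sentence and give them their own, for example:

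> Quarterly numbers of complications will be compared between groups with a negative binomial mixed model (or a GEE with log link and robust standard errors), with the log of time observed as offset and the baseline count as covariate. The effect will be reported as a rate ratio, and the time-by-group interaction will be tested on the log scale.

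Plain Poisson without a patient effect or robust errors should not be substituted, for the reason in step 7. If yes/no per quarter is what is meant, use a logistic mixed model or GEE instead and reword Aim 1 to match. Keep the linear mixed model for ADLs, MSQLI, CSQ-8 and the caregiver burden score. State for which outcomes, and on which scale, the interaction is tested.

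The cost is analysis wording only, with no change to data collection or sample size. The small downside is a slightly more complex fit and a ratio in place of a difference in mean counts.
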